**Sample size**

A pragmatic target of 60 participants with MS (30 in each arm) was estimated based on personal communications with the MS charities recruited for the study and experiences from previous studies [14,15]. This figure aligns with recommended sample sizes for feasibility trials to estimate a parameter for a future RCT [34–36]. This sample size will provide sufficient data to achieve the study aims mentioned above.

Participants with MS will be asked if they are interested in recruiting their employer to the intervention, where they will receive information and advice about MS and employment. Based on previous research studies [14,15], we anticipate that approximately 20% of participants will consent to include their employer.

**Randomisation**

Following the screening procedures, eligible participants who want to participate will receive an email with an electronic consent form using REDCap. Following the completion of the consent form, participants will have the opportunity to complete the baseline assessment electronically (using REDCap) or over the telephone with the lead researcher (BDP).

After completing the consent form and baseline assessment, MS participants will be automatically randomised (1:1 ratio) to MSVR plus usual care (UC) or UC, using adaptative randomisation with minimisation through a computer. The MSVR champions will receive an automatic email informing them of the group allocation.

**Blinding**

Due to the nature of the intervention, the MSVR champions and the mentor will not be blinded to the intervention group of the participants. Participants will not be blinded to the intervention group allocation. The teams at the MS charities will not be able to predict allocation group when referring participants to the study.

Follow-up data will be collected, wherever possible, using REDCap. For participants who prefer to complete the questionnaire via post or telephone, a researcher, blinded to allocation group will collect the data. A form will be developed to record whether the researcher was unblinded during the data collection process.

The researcher supporting the recruitment of participants and conducting the data analysis will be blinded to the group allocation. Other research team members not involved in the direct management of the feasibility trial will remain blinded to group allocation until data collection concludes.

**Intervention adherence and fidelity measures**

Intervention adherence will be measured using the “intervention content forms”. MSVR champions will be trained to complete an intervention content form at the end of each session, reporting the modality of the session, topics discussed, length of time spent discussing each topic, and time spent by MSVR champion completing actions after the session (e.g., liaison with other professionals, reviewing forms, etc). Additionally, an “intervention summary form” form will capture the number of sessions completed by the participants and the number of sessions booked and cancelled (and reasons, if provided).

An intervention fidelity checklist will monitor whether the MSVR champions deliver the intervention as intended. MSVR champions will be asked to video or audio-record 10% of the intervention sessions to explore whether the intervention is being delivered as intended. The lead researcher will analyse the session's content compared to the data recorded in the “session content form” to identify discrepancies.

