**Table 1 Feasibility outcomes and measures**

| Feasibility objectives | Outcomes and measurement |
| --- | --- |
| To assess the feasibility and acceptability of MSVR | **Recruitment**  Length of time to recruit the sample will be calculated using the date of the first and last participant recruited to the feasibility trial  Number of participants with MS screened, meeting the inclusion criteria, recruited and randomised.  Number and reasons of participants not fully meeting the inclusion criteria.  **Retention and engagement**  Number of participants lost to follow-up  Number of participants who withdraw from the intervention  Amount of missing data from questionnaires  Number of participants who complete the initial interview and at least two intervention sessions.  **Intervention delivery**  Hours of support delivered, and number of sessions attended by the participants with MS and employers.  Number of participants who do not attend sessions and number of early dropouts  Hours of support delivered per intervention component and number of participants completing the intervention as structured.  Number of mentoring sessions attended by each MSVR champion.  MSVR champions attendance to training and barriers to delivering the intervention within existing services.  **Acceptability**  Feedback on the intervention content, delivery mode, and structure. |
| To plan for a fully powered trial] | **Selection of primary outcome measure**  Determined by importance of different outcome measures, response rates, and missing data of outcome measures on questionnaires, and preliminary effect size estimates of the outcome measures.  **Sample size**  To estimate the standard deviation of the continuous primary outcome measure with a 95% confidence interval, including lost to follow-up and data completeness.  **Intervention cost**  Cost of MSVR champions and mentor’s time. |

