**Data analysis**

The study's quantitative data will be analysed using SPSS version 27.0 (Statistical Package for Social Sciences) following a predefined statistical analysis plan.

*Recruitment*

Data related to the number of eligible people, recruited, retained for the study (i.e., completion of interview and at least one intervention session), and completion rates of questionnaires will be analysed using descriptive statistics with 95% confidence intervals (CI) (where applicable).

*Demographic and baseline characteristics*

Demographic and baseline characteristics will be presented using descriptive statistics such as mean (standard deviation), median (interquartile range), or percentages to represent frequency. The type of descriptive statistic will vary according to the type of variable (e.g., continuous, ordinal, dichotomous, etc.). We will present both the overall and within groups descriptive statistics. We will explore the level of MS severity among participants recruited in the intervention and control group to understand which participant groups are expressing an interest in this support.

*Feasibility measures*

We will use the CONSORT diagram to report data regarding eligible individuals, participants screened, recruited (per month and per site), randomised, and lost to follow-up.

We will report the time to recruit the target sample, possible recruitment issues, the number of participants who book and attend the initial interview, the number of sessions booked and cancelled, hours of support received, topics addressed, withdrawal and follow-up rates, reasons for dropout (if provided), and the number of employers recruited. The hours of support received per participant will be used to determine the workforce needed for a future RCT.

Participants who drop out during the study will be asked (where possible) why they are dropping out and if they are still interested in completing the end of intervention interview and remaining assessments for the trial.

*Outcome measures*

All outcome measures will be summarised using descriptive statistics (as reported for the demographic characteristics) for all time points for the intervention group and control.

*Economic evaluation*

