The cost of delivering MSVR will be estimated from the time MSVR champions spent participating in the training, attending mentoring sessions, and providing the intervention (measured with the session content forms). Data regarding the hourly rate of MSVR champions will be obtained from the MS charities participating in the feasibility trial.

We will also estimate the cost of the mentoring support based on the hourly rate of the mentors and hours of training, mentoring, and administrative support provided.

*Interviews*

The interviews will be digitally audio-recorded, transcribed verbatim, and analysed on NVivo v14.0. Interviews will be analysed thematically [37] using a hybrid deductive and inductive approach to develop codes and themes [38]. This analysis involves five steps (familiarisation with the data, generation of initial codes, generating themes, reviewing potential themes, and defining and naming themes) [39]. Any disagreements will be discussed with a third researcher (RdN).

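### Champion time lost to appointments missed without cancellation has no stated route into the delivery cost or the workforce estimate, and non-attendance is not recorded as a category of its own

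*Protocol*

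**What the plan says.** Table 1 of the Protocol lists, under intervention delivery, "Hours of support delivered, and number of sessions attended by the participants with MS and employers" and "Number of participants who do not attend sessions and number of early dropouts". Intervention delivery is one of the domains of the primary feasibility outcomes. Intervention cost, listed in the same table under planning the full trial, is the cost of champion and mentor time.

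The section on intervention adherence and fidelity measures describes two forms:

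- The content form: "MSVR champions will be trained to complete an intervention content form at the end of each session". Its time items are "length of time spent discussing each topic, and time spent by MSVR champion completing actions after the session".
- The summary form, which "will capture the number of sessions completed by the participants and the number of sessions booked and cancelled (and reasons, if provided").

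Data analysis, under feasibility measures, plans to report "the number of participants who book and attend the initial interview, the number of sessions booked and cancelled, hours of support received", and says that the support hours each participant received will set the workforce for the future RCT. Under economic evaluation, champion time consists of training, mentoring sessions and "providing the intervention (measured with the session content forms"). The mentor's cost, by contrast, includes administrative support hours.

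**The concern.** A costing source that comes into being only when a session takes place cannot record time spent on a session that did not. If participants miss appointments without cancelling, the champion may still wait, try to make contact and rebook. Apart from follow-up entered on another session's form, that time reaches neither the delivery cost nor the workforce figure. The error runs in one direction and grows as attendance worsens, which is when the funder of a full trial most needs the true figure. It also cannot be repaired at analysis, because minutes not recorded at delivery are lost.

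The second, smaller matter is the count. Table 1 asks how many participants do not attend sessions, but no form as described names a missed session as something distinct from a cancelled one.

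**Working it through.** The Protocol states no no-show rate, session length, hourly rate or cost, so there is no figure of its own to reproduce. The check is a trace of the text, followed by an illustration.

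**Trace 1, cost and workforce**

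1. Delivery time for the cost comes from the session content forms (Data analysis, economic evaluation).
2. Champions "complete an intervention content form at the end of each session" (Intervention adherence and fidelity measures). No session means no form.
3. The form's time items are time per topic and time on follow-up actions. Neither is an item for a missed appointment.
4. The workforce figure rests on support hours received (Data analysis, feasibility measures). A missed appointment adds none.
5. Result: waiting time, and any chasing or rebooking not booked as follow-up to another session, is absent from both. A participant who never attends generates no content form at all.

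**Trace 2, the non-attendance count**

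1. Table 1 counts participants who do not attend.
2. The summary form is described as holding sessions completed, booked and cancelled.
3. If these are three separate counts, unattended = booked - cancelled - completed. With made-up counts of 10 booked, 2 cancelled and 7 completed: 10 - 2 - 7 = 1. A participant with a positive remainder is identified.
4. If the phrase about booking and cancelling denotes one count (sessions booked and then cancelled), the subtraction cannot be done. If no-shows are logged as cancellations, the remainder is zero and they disappear into the cancellations.
5. Result: derivable on one reading, not on others. The text does not choose.

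**Illustration of size**

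Inputs from the Protocol: 30 participants in the MSVR arm (Sample size); up to 10 hours of support each after the initial interview (Intervention: MSVR). The ceiling on this contact time is 30 x 10 = 300 hours.

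Assumptions, none of them in the document: one-hour sessions; r = proportion missed among sessions not cancelled, 5% to 20%; t = champion hours lost per missed session, 0.25 to 1.

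Missed sessions per attended session = r/(1 - r). Omitted time as a share of attended time = t x r/(1 - r).

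| r | t (hours) | Share of attended time | Hours omitted, out of 300 attended |
| --- | --- | --- | --- |
| 5% | 0.25 | 0.25 x 0.05/0.95 = 1.3% | 3.9 |
| 10% | 0.5 | 0.5 x 0.10/0.90 = 5.6% | 16.7 |
| 20% | 0.5 | 0.5 x 0.20/0.80 = 12.5% | 37.5 |
| 20% | 1 | 1 x 0.20/0.80 = 25.0% | 75.0 |

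The share does not depend on the number of sessions. The hours do, and they are upper values because they suppose that every participant uses all 10 hours.

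**The case against.** The strongest reply concerns the count. A reader might infer that the Table 1 non-attendance outcome will be miscounted. The document does not show this. The outcome counts participants, and on the natural reading of the summary form, as three separate counts, anyone whose bookings exceed completions plus cancellations can be picked out. One might answer that rescheduling spoils the subtraction by adding a booking without a completion. That supposes that the first slot is not logged as cancelled, which the Protocol does not say. Attendance at the initial interview is reported directly. What stands against the plan here is ambiguity, not a demonstrated error.

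Second, the forms are not reproduced and may hold more items than the prose lists. That is fair, so the point rests on what the text describes. The costing rule, however, is stated explicitly and names one source for delivery time.

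Third, not all the time need be lost. Chasing or rebooking could be entered as follow-up on an earlier session's form, and remote delivery by existing charity staff means that a missed slot can be used for other work. Both narrow the gap. Neither gives waiting time a place, neither helps for a participant who never attends, and nothing tells champions to record chasing in this way.

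Fourth, the magnitude is wholly assumed, and 25% needs the worst value of both inputs. This stands. It would also be wrong to read 25% as the bias in the reported cost: the denominator is attended session time, while the cost also includes follow-up actions, training, mentoring and the mentor's time.

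Finally, no progression criterion uses no-show counts or cost, and both cost and workforce serve the planning of the later trial. This bears on the importance of the point, not on whether it is right.

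**Conclusion.** The costing point holds. As the Protocol describes it, champion time on appointments missed without cancellation is left out of the delivery cost and the workforce estimate, except for whatever chasing or rebooking happens to be entered on another session's form. Both estimates are biased downwards. The document does not allow the amount to be calculated. About 1% to 25% of attended session time is an illustration that rests on assumed no-show rates, minutes lost and session length, with 5.6% at 10% missed and 30 minutes lost. As a share of total intervention cost the figure would be smaller.

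On the count, the supported conclusion is limited: non-attendance is not recorded separately from cancellation and can at best be derived by subtraction, on one of several readings of the form.

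The point is minor. It is worth making because the bias has a known direction, the missing data cannot be recovered later, and the remedy is cheap.

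**What to change.** 1. On the existing intervention summary form, add a category for sessions not attended without notice, distinct from cancelled and from rescheduled. Beside it, record the champion minutes lost, with an instruction not to repeat time already entered as follow-up on a content form.
2. Take the Table 1 non-attendance item from that category instead of from a subtraction.
3. In Data analysis, under economic evaluation, add these minutes to the content-form time when costing delivery. Under feasibility measures, add them to the support hours when estimating the workforce.

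The cost is two fields on a form already in use, one extra line in the costing, slightly more form-filling for champions and a somewhat higher reported delivery cost. Design, sample size and progression criteria are unaffected.

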**Aims**

The primary aim is to assess the feasibility and acceptability of conducting a multicentre, parallel-group RCT comparing MSVR delivered to participants recruited from MS charities with existing services offered by the charities alone. More specifically, we will focus on:

1. Recruitment: To assess the length of time to recruit the sample planned, the recruitment rate, the proportion of eligible patients recruited, reasons for non-recruitment, and the appropriateness of study characteristics such as inclusion and exclusion criteria.
2. Retention and engagement: To estimate the proportion of participants lost to follow-up and the reasons for loss to follow-up, withdrawal rates, data completeness, and participants’ compliance with MSVR and identify factors affecting compliance.
3. Intervention delivery: To assess feasibility of delivering up to 10 hours of VR over 6 months, intervention fidelity, intervention adherence, feasibility of delivering VR alongside existing services of the charities, and practical issues related to intervention delivery.

The secondary aims are to determine parameters for a sample size calculation for a future large-scale RCT and explore the mentoring and training needs of the MSVR champions (i.e., employees from MS charities recruited to deliver the intervention) recruited for the study.

This study includes an embedded mixed methods process evaluation, the aims of which are to understand acceptability and usefulness of:

- MSVR for people with MS, employers, and MSVR champions.
- study procedures to MS charities and participants.
- MSVR training manual, sessions, and mentoring support.

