**Primary and secondary outcomes**

The primary outcomes assess the feasibility and acceptability of delivering MSVR within the context of MS charities by measuring recruitment, retention and engagement, and intervention delivery.

Secondary outcomes refer to determining the parameters for a fully powered trial, including selecting a primary outcome measure, sample size estimation, intervention costs, and identifying intervention improvements and further training needs of MSVR champions. The feasibility outcomes are summarised in Table 1.

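### The protocol sets no rule for which 10% of sessions are recorded, so champions may choose which of their own sessions are reviewed for fidelity

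*Protocol*

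**What the plan says.** The protocol's Aims section places fidelity in item 3 of the primary aim: "To assess feasibility of delivering up to 10 hours of VR over 6 months, intervention fidelity, intervention adherence". The section on primary and secondary outcomes says feasibility and acceptability will be assessed "by measuring recruitment, retention and engagement, and intervention delivery".

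The section on intervention adherence and fidelity measures describes three sources of information:

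- **Champion forms.** "MSVR champions will be trained to complete an intervention content form at the end of each session". These cover modality, topics and time per topic, and are the champion's own account.
- **Checklist.** "An intervention fidelity checklist will monitor whether the MSVR champions deliver the intervention as intended". Who completes it, and for which sessions, is not stated.
- **Recordings.** "MSVR champions will be asked to video or audio-record 10% of the intervention sessions", with the stated purpose of exploring whether delivery matches what was intended. Then: "The lead researcher will analyse the session's content compared to the data recorded in the “session content form” to identify discrepancies".

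No section gives a rule for choosing the recorded sessions, whether random, consecutive, stratified or set by the researchers. None gives a quota per champion, charity, participant or stage of the case. By contrast, the Process Evaluation section does state how interviewees are sampled (purposively) and which kinds of participant are sought.

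**The concern.** The only people given the recording task are those whose work the recordings are meant to check. With no selection rule, a champion could follow the protocol to the letter and record sessions expected to go well, or sessions with easier participants. The 10% could also be met overall with some champions, or the later part of cases, not covered at all.

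Two uses of the recordings are exposed:

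1. **The picture of fidelity.** If well-delivered sessions are more likely to be recorded, delivery looks better than it is.
2. **The check on the forms.** The recordings are compared with the content forms, and forms are the source for unrecorded sessions. The Economic evaluation section takes delivery time from the session content forms (taken here to be the same form as the intervention content form), and the Data analysis section uses hours of support to plan the workforce for a future trial. If recorded sessions are not typical, agreement between form and recording there may not carry over to the rest.

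Which sessions are recorded is settled while sessions are being delivered. It is a data-collection rule that a statistical analysis plan would not normally fix, and no analysis can recover a session that was never recorded.

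**Working it through.** The protocol states no fidelity figure, threshold or number of recordings, so there is nothing to reproduce. The check has three parts.

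**1. Is there a selection rule anywhere?** The whole protocol was read for one. None was found. The fidelity section says who makes the recordings and what share of sessions is recorded, and stops there.

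**2. How many recordings would there be?** From the Sample size section, the MSVR arm has 60 / 2 = 30 participants. The number of sessions per participant is not given; 2 to 10 is assumed.

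- Sessions: 30 × 2 = 60 to 30 × 10 = 300.
- Recordings at 10%: 6 to 30.
- Number of champions: not given. Five or six is assumed, from the five champion interviews planned and the limit of six charities. That gives 6 / 6 = 1 to 30 / 5 = 6 recordings per champion.

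Precision is low under any selection method. Exact (Clopper-Pearson) 95% intervals are 0.40 to 0.97 for 7 of 9 faithful sessions (9 recordings corresponds to 3 sessions per participant) and 0.61 to 0.92 for 24 of 30. Random selection would not cure this; it is a separate matter from selection.

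**3. What could selection do?** Let p be the true share of sessions delivered as intended, and w how many times more likely such a session is to be recorded than one that is not. Then

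observed share = w·p / (w·p + 1 − p).

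| True p (assumed) | w = 1 | w = 2 | w = 3 |
|---|---|---|---|
| 0.60 | 0.60 | 1.2 / 1.6 = 0.75 | 1.8 / 2.2 = 0.82 |
| 0.70 | 0.70 | 1.4 / 1.7 = 0.82 | 2.1 / 2.4 = 0.88 |
| 0.80 | 0.80 | 1.6 / 1.8 = 0.89 | 2.4 / 2.6 = 0.92 |

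The first column is selection independent of the champion: on average the observed share equals the true one. The other columns show what a preference for better sessions would do. Neither p nor w comes from the protocol, and the protocol does not define a faithful-or-not score per session. The table shows how the mechanism works; it does not estimate the bias in this trial.

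**The case against.** The strongest reply is that silence is being read as a bad rule. The text says who operates the recorder; it does not say who picks the session, and being asked to record is compatible with the research team naming the sessions. The sentence could also mean that each champion records 10% of their own sessions. This stands: a reader might infer that the protocol lets champions choose by design, but it only leaves the matter open.

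A reader might also infer that a primary outcome estimate is likely to be biased. The documents do not support that. Fidelity is in the primary aim, but Table 1 has no recording-based fidelity measure; its nearest items are hours per component and the number completing the intervention as structured. The progression criteria omit fidelity, no fidelity threshold is set, and the stated purpose of the recordings is exploratory. The illustrative percentages follow from their assumptions and cannot be quoted as the expected error.

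Three further points hold in part:

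- Content forms exist for every session, so recorded and unrecorded sessions can be compared on modality, topics and time. That helps, but the forms are the champions' own reports, which the recordings are meant to test.
- Monthly mentoring and the end-of-intervention interviews also give information on delivery. Mentoring works from cases discussed with the champions, and the interviews address acceptability and engagement; neither checks session content directly.
- A session that goes well need not have a more accurate form, and a champion who knows a session is recorded may behave or document differently. So the effect on the form check is uncertain in direction, and selecting sessions centrally does not remove the effect of being recorded.

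**Conclusion.** The point holds in a limited form. The protocol assigns recording to the people being assessed and fixes neither who selects the sessions nor that each champion is covered. The recordings are the only described check on session content that clearly does not rest on the champion's own account, since the checklist has no stated rater. As written, the recorded sample could therefore flatter fidelity, and it may not represent the accuracy of the forms.

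The upward direction for fidelity is a reasonable inference, resting on the assumption that champions who choose would tend to favour their better sessions. Its size cannot be derived from the protocol. With an assumed 6 to 30 recordings, a few chosen sessions could change the impression given. Because no go or stop decision depends on the recordings, this is a modest, inexpensive improvement, best made before sessions are delivered.

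**What to change.** Add to the section on intervention adherence and fidelity measures that:

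- the research team selects the sessions to record from a computer-generated list by participant and session number;
- each champion has at least one or two sessions selected, with a spread over early and late sessions where numbers allow;
- if a participant declines recording, the refusal is logged and the next listed session is taken;
- sessions recorded are reported against sessions selected, for each champion.

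Full stratification is not advised. With five or six champions (assumed), crossing champion with early or late gives 10 to 12 strata, which 6 recordings could not fill and 30 would fill only thinly. Refusals mean the recorded set will not be perfectly random, which is why selected and recorded sessions should both be reported.

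Cost: a short addition to the text, a simple list, and minor scheduling work, including a few replacement sessions. The number of recordings and the review workload stay the same.
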